#### Randomization

Patients will be randomized after informed consent is obtained and it is confirmed that all inclusion and no exclusion criteria are met, prior to the patient-clinician discussion of treatment options and patient risk. Allocation will be concealed by means of an online password-protected randomization algorithm designed using Medidata Balance™ Medidata Solutions, New York City, USA. Patients will be dynamically stratified
[19] by enrolling by site, age and sex because of the known association of age and sex with cardiovascular risk and the availability of these data at the time of enrollment. Allocation will be based on a 1:1 ratio between the intervention and usual care arms. Though we will not be able to blind patients and clinicians to use of the decision aid, we will blind the investigators and individuals not involved in providing care to the patient allocation.

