#### Usual care

For patients randomized to the usual care arm the clinician will discuss the results of diagnostic investigations and management options with the patient in that clinician’s usual fashion. The patient’s risk will be calculated using the QPTP calculator for study purposes, however, the patient and clinician will be blinded to the QPTP-structured risk assessment and the corresponding decision aid in this arm. As in the intervention arm, the clinician-patient disposition discussion will be video and audio recorded to assess the degree to which the clinician engages the patient in the decision-making process and to monitor for contamination in the control arm.

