#### Statistical considerations

In order for the study findings to maximally impact practice and policy, they will need to be adequately powered to detect differences in outcomes of interest to each of the stakeholders (patients, clinicians, shared decision-making research experts, and healthcare payers). We will have sufficient funding to enroll 930 patients, accounting for a loss to follow-up rate as high as 5% (there was 2% lost to follow-up in our pilot trial)
[11], we anticipate having complete data on 884 patients. Table 
1 shows the anticipated power we will have to detect differences in each of the patient and stakeholder-important outcomes on completion of the trial.

**Table 1 T1:** Anticipated power to detect patient and stakeholder-important outcomes on completion of the trial

**Outcome (n = 884)**	**Usual Care***	**Decision Aid***	**Difference**	**Power**
**Patient knowledge**	44% (23.3)	60% (20.9)	16% (9.5%, 22.5%)	99%
**Patient engagement in the decision-making process (n = 221)**	7.0 (5.5)	26.3 (8.2)	19.3 (18.4, 20.2)	99%
**Decisional conflict†**	35.9 (18.9)	22.3 (21.1)	13.6 (11.0, 16.2)	99%
**Trust in the physician**	79.3 (19.9)	83.4 (19.8)	4.1 (1.5, 6.7)	86%
**Patient satisfaction with the decision made (% agree or strongly agree they are satisfied)**	69.7 (25.6)	80 (25.6)	10.3 (4.6%, 16.0%)	99%
**Safety (major adverse cardiovascular events)‡**	0%	0%	0% (−−)	78%
**Proportion of patients admitted for cardiac testing**	77%	67%	10% (4.1, 15.9)	90%
**Healthcare utilization**	8.3 (0.8)	7.0 (0.7)	1.3 (1.2, 1.4)	99%

*Estimates were determined from our completed pilot randomized trial [11].

†Lower decisional conflict scores indicate less conflict experienced by patients related to feeling uninformed.

‡Non-inferiority, one-sided test with alpha = 0.05 with a maximum difference of 5%.

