We will use standard techniques appropriate for patient-randomized trials, with each outcome compared between study arms using t-tests for continuous outcomes and chi-square tests for dichotomous outcomes. Rather than assume the intervention effect is independent of the study site where the patient is seen or of the clinician who sees them, we will assess intra-site and intra-clinician correlations. We will then stratify all tests on the study site unless the intra-clinician correlation is non-trivial, in which case we will stratify on a clinician basis. We will calculate differences and their confidence intervals using standard techniques for continuous and dichotomous data. If there are differences in baseline characteristics between the two study groups, these will be accounted for using regression models that will include an indicator for study arm. Finally, we will analyze clinician surveys using regression models with robust standard errors to account for the repeated measures on clinicians.

Descriptive analyses will be performed to describe any potential heterogeneity of treatment effect (HTE) and facilitate synthesis of subgroup results in future meta-analyses. We will conduct descriptive HTE analyses by age, gender, race/ethnicity, quantitative pre-test probability of ACS, level of education, OPTION scores, and study site. The outcomes assessed with HTE analyses will be the same as those assessed in the trial (such as knowledge, engagement, satisfaction, and healthcare utilization). We will also conduct interaction testing to determine the interaction between the decision aid and each pre-specified characteristic.

Resource use will be compared both descriptively and using multivariable models. Descriptive comparison for 30-day utilization will utilize the Wilcoxon rank-sum test to account for the skewness of the outcome measures. The multivariable models for resource utilization will be estimated using the two-part or one-part negative binomial or log gamma regression models. A two-part model will be utilized for outcomes where more than 10% of the subjects have a zero outcome measure. The covariates in the multivariable models will include factors that may not be accounted for in the randomization such as comorbidities and severity of illness. Comorbidities will be measured using the Elixhauser method, which is a commonly used measure for the acute setting

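### Age and sex are balanced at allocation but left out of the main tests, and covariates enter only if baseline differences are observed: a modest loss of precision and a data-dependent model

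*Protocol article*

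**What the plan says.** Under Randomization, the protocol article says that patients are dynamically stratified "by enrolling by site, age and sex because of the known association of age and sex with cardiovascular risk", in a 1:1 ratio.

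Under Statistical considerations, the main analysis has "each outcome compared between study arms using t-tests for continuous outcomes and chi-square tests for dichotomous outcomes". On stratification it says: "We will then stratify all tests on the study site unless the intra-clinician correlation is non-trivial, in which case we will stratify on a clinician". Neither version contains age or sex.

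Regression adjustment is conditional: "If there are differences in baseline characteristics between the two study groups, these will be accounted for using regression models". The article names no covariates for this step and no criterion for a difference.

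Resource use is handled separately, in multivariable models: "The covariates in the multivariable models will include factors that may not be accounted for in the randomization such as comorbidities and severity of illness". Age and sex are not named there. Elsewhere in the statistical section they appear only in the heterogeneity and interaction analyses.

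**The concern.** There are two linked problems.

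**Allocation and analysis do not match.** Balancing on a prognostic factor reduces the true sampling variation of the treatment difference. A test that omits the factor leaves its variance in the error term, so the reported standard error does not show that reduction. Intervals are then wider than they need to be and tests are conservative.

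**The adjustment rule looks at the wrong thing.** In a randomised comparison, baseline differences arise by chance. A rule triggered by them picks covariates for chance imbalance, not for their relation to the outcome. Age and sex, which the authors themselves regard as prognostic, are kept balanced and so are among the factors least likely to trigger it. The model also cannot be known until the arms have been compared at baseline.

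At stake are some precision on the secondary outcomes with limited power headroom and a clear statement of which estimate is primary.

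**Working it through.** **Inputs.** From Table 1 and its lead-in text: 884 patients with complete data, taken as 442 per arm; trust 79.3 (SD 19.9) against 83.4 (SD 19.8), difference 4.1, stated power 86%; knowledge 44% (23.3) against 60% (20.9), stated power 99%; admission 77% against 67%, stated power 90%. Two assumptions are needed. The first is a two-sided alpha of 0.05, because the article states alpha only for the safety row. The second is R², the within-site outcome variance explained by age and sex, which the article does not give. Site is already in the tests, so its share is not lost and does not count.

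**Step 1: reproduce the plan's figures.**
- Trust: SE = √[(19.9² + 19.8²)/442] = 1.335; z = 4.1/1.335 = 3.07; power = Φ(3.07 − 1.96) = 86.7%, against 86% stated. The half-width 1.96 × 1.335 = 2.62 gives the tabulated interval of 1.5 to 6.7.
- Knowledge: SE = √[(23.3² + 20.9²)/442] = 1.489; z = 16/1.489 = 10.7; power above 99.9%.
- Admission: 91.3% without continuity correction. With it, 442 per arm is the sample size for 90%.

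**Step 2: put age and sex in the model.** The SE is multiplied by √(1 − R²), and power = Φ(3.07/√(1 − R²) − 1.96).

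| Assumed R² | SE multiplier | Trust SE | Interval half-width | Trust power |
|---|---|---|---|---|
| 0 | 1 | 1.335 | 2.62 | 86.7% |
| 0.02 | 0.990 | 1.322 | 2.59 | 87.3% |
| 0.05 | 0.975 | 1.301 | 2.55 | 88.3% |
| 0.10 | 0.949 | 1.267 | 2.48 | 89.9% |

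Knowledge power stays above 99.9% throughout.

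**Step 3: the site-stratified test under balanced allocation.** If age and sex are fully balanced, the test statistic has variance 1 − R² instead of 1. The actual type I error is then 2[1 − Φ(1.96/√(1 − R²))], which is 0.048, 0.044 and 0.039 at R² of 0.02, 0.05 and 0.10. Its actual power for trust is Φ((3.07 − 1.96)/√(1 − R²)), which is 86.9%, 87.3% and 87.9%. Against that like-for-like benchmark, adjustment gains about 0.4, 1.0 and 2.0 points. This is smaller than the comparison with 86.7%, because balancing has already delivered part of the benefit.

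**Step 4: simulation.** The set-up was 884 patients minimised on five sites, two age groups and sex, with assignment probability 0.8. There were 2,000 null runs and 1,000 runs at the trust effect per R². The conditional rule screened 10 baseline variables (age, sex and eight others) at p < 0.05.

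| R² | Type I error: site / site+age+sex / conditional | Power: site / site+age+sex / conditional |
|---|---|---|
| 0.02 | 0.048 / 0.052 / 0.049 | 86.4 / 87.1 / 86.1% |
| 0.05 | 0.051 / 0.058 / 0.046 | 86.1 / 86.8 / 86.3% |
| 0.10 | 0.034 / 0.044 / 0.033 | 88.0 / 89.7 / 88.3% |

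The Monte Carlo standard error of a type I error near 0.05 is √(0.05 × 0.95/2000) = 0.005, so only the R² = 0.10 row shows clear conservatism. The conditional rule changed the model in about 30% to 35% of runs. That agrees with 1 − 0.95⁸ = 34% for the eight unbalanced variables alone, so age and sex added almost no triggers. The rule recovered little or none of the power gap.

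**The case against.** The strongest reply is that little hangs on this. The primary outcome has power to spare, no false-positive risk is shown, and the article ties age and sex to cardiovascular risk, not to trust or knowledge, so R² for those outcomes could be near zero. All of that stands and limits the size of the point.

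A second reply is that a condensed article may leave the covariate list, the criterion for a difference and the choice of primary estimate to the SAP. That is fair for those details. But the article states the imbalance trigger as its method, so an SAP that fixed one model would have to replace this text.

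Several stronger readings are tempting and not supported:
- A reader might infer that age and sex can never enter. Dynamic allocation limits imbalance but does not abolish it, and the article allows exclusions after randomization; rarely is the most that can be said.
- A reader might take the tests to be stratified on site alone. The clinician fallback is stated.
- A reader might count everything that site, age, sex and the QPTP (quantitative pretest probability) estimate explain as precision lost. Site is already in the tests, and QPTP is not an allocation factor.
- A reader might suppose that the trigger governs resource use. Those models have their own covariates, and the list is illustrative.
- A reader might suspect outcome-driven model choice because patients and clinicians are unblinded. The trigger concerns baseline characteristics, and investigators and others not giving care are to be blinded to allocation. The article also does not say that the adjusted estimate replaces the unadjusted one.

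**Conclusion.** The point holds as a modest one. The main tests omit two of the three factors used for allocation, and the stated route to adjustment depends on chance imbalance and will rarely admit those two. Where age and sex are prognostic within site, the result is conservative inference and a model that is not fixed in advance. Error rates are not inflated, and the primary outcome's power is unaffected.

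For an assumed within-site R² of 0.02 to 0.10, the standard error falls by about 1% to 5% and power for trust goes from 86.7% to about 87% to 90%. Measured against the site-stratified test's actual power under balance, the gain is about 2 points at most over that range. These sizes rest on the assumed R², a two-sided alpha of 0.05 and equal arms of 442. If age and sex do not predict an outcome, nothing is lost on it, and only the data-dependent choice of model remains.

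**What to change.** - For knowledge, decisional conflict, trust, satisfaction, engagement and admission for cardiac testing, prespecify one primary model with arm, site, age and sex, whatever imbalance is observed. Use linear regression for scores, and logistic or binomial regression with a standardised risk difference for proportions.
- QPTP may be added as an option. It is available in both arms, since in usual care the patient's "risk will be calculated using the QPTP calculator for study purposes". It is not needed to match the analysis to the allocation.
- Retain the planned handling of clinician correlation alongside this model.
- Make imbalance-triggered adjustment and the unadjusted tests supportive only.
- Add age and sex to the existing resource-use models and keep their negative binomial or log gamma form.
- Leave the non-inferiority comparison of major adverse cardiac events unadjusted. Table 1 expects 0% in both arms, so a covariate model could not be fitted reliably.

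The cost is a revised analysis section and some model specification. No new data are needed: site, age and sex are recorded for allocation, and QPTP is calculated for every patient.

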#### Outcome measures

When selecting outcome measures we obtained input from a patient and caregiver representative, clinicians (emergency medicine clinicians and cardiologists), researchers (health services researchers and shared decision-making experts), and a payer representative (Chief Medical Officer of Mayo Clinic Health Solutions). In face-to-face meetings with the patient and caregiver representative it became clear that knowledge was the outcome that was of greatest interest to the patient, so patient knowledge was selected as the primary outcome. Thus, as we did in our pilot trial, we will assess patient’s knowledge regarding their short-term risk for ACS, the potential implications of cardiac testing, the available management options, and the potential risk of radiation exposure through a post-visit survey administered immediately after the clinical encounter
[11].

We will also assess a number of secondary outcomes, including patient engagement in the decision-making process, as measured by the OPTION (observing patient involvement) scale
[21]; the degree of conflict patients experience related to feeling uninformed, as measured by the Decisional Conflict Scale (DCS)
[22]; trust in the physician measured via the Trust in Physician Scale (TPS)
[23]; patient satisfaction with the decision made, via a Likert scale on the post-visit survey; and safety as determined by the prevalence of Major Adverse Cardiac Events (MACE) within 30 days of the ED visit.

Consistent with recommendations in a recently published consensus document on ACS research in emergency departments
[24], we will define MACE as AMI
[25], death due to a cardiac or unknown cause, emergency revascularization, ventricular arrhythmia, or cardiogenic shock. We will exclude MACE that occurs during the index admission to the ED but rather focus on events occurring after discharge, in the outpatient setting, which could have potentially been avoided or diagnosed in the ED or hospital. This approach avoids having to adjudicate whether MACE occurring in the ED or hospital were ‘missed’ based on a post-hoc review of potentially incomplete medical records. We will collect data on all MACE that occur up to 45 days from the index ED visit as this is the follow-up interval assessed by the QPTP instrument

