#### Data collection

Data documenting the process of screening for potentially eligible participants, application of the eligibility criteria (including the reason for each exclusion), the variables entered into the pretest probability calculator, the arm to which each patient is randomized, and other information best collected in real time will be recorded by study coordinators using a standardized case report form (Additional file
2). Patients’ preferences for understanding numerical information and their preferred approach to participation in medical decision-making will be assessed by a survey administered prior to the clinical encounter (Additional file
3).

Immediate post-visit surveys will collect data on patient knowledge, decisional conflict, patients’ trust in their physician, and patient satisfaction with the decision made (Additional file
4). The degree to which clinicians engage patients in the decision-making process will be assessed by having two trained team members independently review videos of the clinician-patient disposition discussion and apply the OPTION scale
[21].

The patient will be contacted 45 days after enrollment via telephone (primary method of contact) for assessment of safety. If the primary method of contact is not successful the study coordinator will subsequently contact the patient utilizing a secondary method of contact specified by the patient at the time of consent (such as email, a secondary phone number, or mail) for a follow-up assessment. Safety will be assessed using a standardized phone follow-up script to determine whether a MACE occurred and, if so, the date of the event (Additional file
5). Events occurring within 45 days will be recorded to ensure consistency with the duration of follow-up used in the development of the QPTP instrument
[15] and MACE within 30 days will be reported in accordance with standardized reporting guidelines for risk stratification studies of ED patients with potential ACS
[26].

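### OPTION score, measured after randomisation and itself a secondary outcome, is listed as a treatment-effect modifier; subgroup and interaction results by OPTION cannot be read as effect modification.

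*Protocol article*

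**What the plan says.** All references are to the Protocol article.

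- **Heterogeneity list (Statistical considerations).** The characteristics are age, gender, race/ethnicity, pre-test probability of ACS, "level of education, OPTION scores, and study site". The analyses are introduced as descriptive and intended to support later meta-analyses. The plan then adds: "We will also conduct interaction testing to determine the interaction between the decision aid and each pre-specified characteristic".
- **Outcomes for these analyses (same section).** "The outcomes assessed with HTE analyses will be the same as those assessed in the trial (such as knowledge, engagement, satisfaction, and healthcare utilization").
- **Status of OPTION (Outcome measures).** It is a secondary outcome: "patient engagement in the decision-making process, as measured by the OPTION (observing patient involvement) scale".
- **How OPTION is obtained (Data collection).** Two trained team members "independently review videos of the clinician-patient disposition discussion and apply the OPTION scale".
- **Timing (Randomization).** Patients are randomised "prior to the patient-clinician discussion of treatment options and patient risk".
- **Expected effect on OPTION (Table 1).** 7.0 (5.5) under usual care, 26.3 (8.2) with the decision aid, difference 19.3, n = 221, power 99%.

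**The concern.** Age, gender, race/ethnicity, pre-test probability, education and site are not changed by the allocated arm. OPTION is different: it scores the very conversation that the decision aid is designed to change. Comparing arms among patients with similar OPTION scores means comparing usual-care encounters that were unusually engaging with decision-aid encounters that were ordinary or unusually poor. Those groups are no longer exchangeable. Any part of the benefit that runs through engagement is also removed.

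At stake is how these results are read. A treatment effect by OPTION level, or a treatment-by-OPTION interaction, would sit in the same table as legitimate baseline modifiers and be available to meta-analysts on the same footing. Because engagement is among the outcomes of these analyses, a literal reading would also have OPTION analysed by OPTION.

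**Working it through.** **Inputs.** From Table 1: OPTION 7.0 (5.5) and 26.3 (8.2), n = 221; knowledge 44% (23.3) and 60% (20.9), n = 884. Allocation is 1:1. Assumed, because the article does not give them: normal scores, a pooled-median split (illustrative only), two-sided alpha 0.05, and a within-arm OPTION-knowledge correlation r of 0 to 0.5, the same in both arms.

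**1. The plan's own figure.** Pooled SD = sqrt((5.5² + 8.2²)/2) = 6.98. With 110.5 per arm and a difference of 19.3, power exceeds 99.9%, which is consistent with the stated 99%.

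**2. Separation of the arms.** The standardised shift is 19.3/6.98 = 2.76. The two normal densities cross at about 15.7 and overlap by 15.5%; gamma densities with the same means and SDs overlap by 14.8%.

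**3. Pooled-median split.** The median c satisfies (c - 7.0)/5.5 = (26.3 - c)/8.2 = 19.3/13.7 = 1.409, so c = 14.75. Then 92.05% of usual care and 7.95% of the decision-aid arm fall below it.

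- n = 221: 110.5 × 0.0795 = 8.8 against 110.5 × 0.9205 = 101.7.
- n = 884: 442 × 0.0795 = 35 against 442 × 0.9205 = 407.

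Both sizes are shown because the number of recordings is uncertain. Table 1 gives n = 221 for this row, but its printed interval of 18.4 to 20.2 equals 19.3 ± 1.96 × sqrt((5.5² + 8.2²)/442), which corresponds to 884 patients.

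**4. Engagement by OPTION.** Truncated-normal means use φ(1.409) = 0.1479; 0.1479/0.0795 = 1.861 and 0.1479/0.9205 = 0.161.

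- Low stratum: (26.3 - 8.2 × 1.861) - (7.0 - 5.5 × 0.161) = 11.0 - 6.1 = 4.9.
- High stratum: (26.3 + 8.2 × 0.161) - (7.0 + 5.5 × 1.861) = 27.6 - 17.2 = 10.4.

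The expected 19.3-point difference shrinks to 4.9 and 10.4 purely by construction.

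**5. Knowledge by OPTION.** Let every patient gain exactly 60 - 44 = 16 points. Pooled SD = sqrt((23.3² + 20.9²)/2) = 22.13. The expected within-stratum difference, the same in both strata, is 16 - 22.13 × r × (1.861 - 0.161) = 16 - 37.6r. The last column is the simulated rejection rate of a test of arm × continuous OPTION at n = 221; the ranges reflect repeated simulations.

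| r | Apparent effect in each stratum | Rejection rate |
|---|---|---|
| 0 | 16.0 | about 5% |
| 0.2 | 8.5 | 8-9% |
| 0.3 | 4.7 | 14-16% |
| 0.5 | -2.8 | 37-39% |

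The interaction test based on the median split stays near 5% in this set-up; its stratum estimates are what is distorted. The continuous test rejects too often because an equal correlation with unequal OPTION SDs implies unequal slopes. At r = 0.3 these are 22.13 × 0.3/5.5 = 1.21 knowledge points per OPTION point under usual care and 22.13 × 0.3/8.2 = 0.81 with the aid. If the slopes were equal, that test would hold its level.

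**The case against.** The analyses are called descriptive, OPTION is one of seven characteristics, and nothing in the primary, secondary, safety or power calculations depends on it. That stands, and it limits how serious the point is. It does not remove it: the interaction tests promised for every listed characteristic are formal tests, and a descriptive label does not make a post-randomisation variable a modifier.

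The bias depends on a correlation that the documents do not give, and at r = 0 there is none for outcomes other than engagement. That is correct, which is why a range is shown. Likewise, 9 against 102 rests on a split that the plan does not specify and on n = 221.

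A reader might infer that the plan would falsely show the aid working only, or failing, in highly engaged patients. The documents do not support that. In the set-up above, the median split attenuates both strata equally, and a false interaction appears only with continuous OPTION. OPTION also rates how far clinicians involve patients, so a high score does not identify an engaged type of patient.

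Analysing OPTION by OPTION is a literal reading of a sentence that gives its outcomes as examples. It may be loose drafting that nobody would carry out.

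**Conclusion.** The point holds. OPTION is a post-randomisation outcome named as an effect modifier, and the article offers no baseline, clinician-level, mediation or principal-stratum reading of it. Subgroup estimates and interaction tests by OPTION cannot be interpreted as effect modification. That follows from the timing and status of the measure and needs no assumption.

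The numerical size does rest on assumptions. The 15% overlap assumes normality. The stratum counts assume a pooled-median split and 221 to 884 recordings. The distortion of a constant 16-point knowledge benefit, from none to a reversal of about -3, assumes a within-arm correlation of 0 to 0.5, equal in both arms.

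A reader might infer that the trial's main result is threatened. It is not: the overall comparison of knowledge, the engagement comparison between arms and all figures in Table 1 are untouched. This should be corrected before analysis, but the trial's conclusions on its main outcomes do not depend on it.

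**What to change.** Delete OPTION scores from the heterogeneity list in Statistical considerations, and so from the interaction tests. Six characteristics remain, with six interaction tests per outcome instead of seven.

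If the role of engagement is of interest, report OPTION in a separate analysis labelled exploratory mediation, process or fidelity. The videos are already meant to serve fidelity monitoring.

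The pre-encounter survey records numeracy preference, and "their preferred approach to participation in medical decision-making will be assessed by a survey administered prior to the clinical encounter". These items could be added as optional baseline modifiers if they are confirmed to be collected before randomisation; the article says only before the encounter. They describe what patients prefer, not what clinicians do, so they are different constructs and not a substitute for OPTION.

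The cost is one wording change. No sample size, power figure or data collection changes.
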